#### Concealment mechanism {16b}

Conditions are concealed within a digital randomization key that is only accessible to unmasked staff.

#### Implementation {16c}

Stratification information will be sent to the study statistician via Research Electronic Data Capture (REDCap). The study statistician will complete the randomization, the TMS supervisor will verify the randomization, and then the TMS operators will be informed of protocol type (cTBS or iTBS) and coil (active vs. sham coils are concealed with coded letters or colors). A separate active coil will be used for RMT determination to enhance masking.

### Assignment of interventions: Blinding

#### Who will be blinded {17a}

People who will be masked to TMS status (active vs. sham) are participants, caregivers (if applicable), and study staff involved in the clinical assessments (independent evaluators, IEs), coding the ERP videos, delivering ERP therapy, delivering TMS, and collecting the MRI data. The staff involved in the clinical assessments and coding the ERP videos will not be present for a given participant’s TMS + ERP sessions to ensure masking to overall treatment progress. In Phase I, some people will necessarily be aware of cTBS vs. iTBS allocation (TMS operator, participants, and caregivers present for TMS) but will remain masked to active vs. sham status. In phase 2 these individuals will be fully masked. After treatment, forms assessing masking adequacy will be given to masked staff who conduct TMS, ERP, and assessment visits. Unmasked staff will be the study statistician and the TMS site supervisor.

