### Strategies to improve adherence to interventions {11c}

Coil placement during TMS administration will be continually monitored using BrainSight (BrainSight 2.3.5, Rogue Research, Montreal, Quebec, Canada). All ERP sessions will be video recorded and 100% will be coded using the Exposure Process Coding System (6) to measure compulsions and therapist and patient adherence. Participant compliance with ERP assignments and in-session tasks will be tracked by the ERP therapist at each session.

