### Procedure for unblinding if needed {17b}

Intentional unmasking of TMS status (active vs. sham) will be allowable if deemed necessary for participant safety, to address a TMS device issue, or another unforeseen situation in which status knowledge is essential for study conduct. Only individuals deemed most critical for addressing the situation will be unmasked. IEs will not be intentionally unmasked.

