### Measure procedures

#### Exposure Process Coding System (EPCS)

EPCS [6, 36] is an observer-rated, microanalytic, time-stamped coding system that uses Noldus Observer software to capture in-session behaviors as they occur on video. EPCS measures the frequency and duration of youth compulsions during exposure tasks, along with codes measuring therapist behaviors (which serve as an index of treatment fidelity) and youth distress levels (youth-reported and observer-rated; which can index exposure learning). Bachelor’s degree-level study coders will code 80% of video-taped session data. Coders will be trained and monitored to prevent drift. Training will include background reading, group discussions, practice coding with feedback, and practice coding to criterion. Raters must attain reliability on practice videos (*k* > 0.80) before coding study videos. If coder drift is detected, re-training will occur and remaining study videos will not be coded until the reliability criterion is re-established. Ten percent of sessions will be double-coded to assess reliability.

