##### Primary outcome (compulsion duration)

Following procedures outlined for this outcome in Phase 1, a linear regression model will assess whether compulsion duration differs by treatment group. A linear regression model will also be used with the outcome of interest being the percent change in OCD symptom severity (C/YBOCS) pre- to post-treatment. The primary predictor will be a group indicator for sham vs active rTMS. Compulsion duration and its interaction with the group indicator will be included as potential mediators for the dependent variable. Total exposure duration will be a covariate in both analyses.

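### Absence from sessions cannot mask the video coders to treatment progress, because they code recordings of those sessions; the main exposure is the Phase 2 mediation analysis

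*Protocol article*

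**What the plan says.** Under Who will be blinded {17a}, one sentence covers two groups, the staff doing clinical assessments and the staff coding the ERP videos. It says that those "coding the ERP videos will not be present for a given participant’s TMS + ERP sessions to ensure masking to overall treatment progress". The same section masks both groups to active versus sham.

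Other sections describe what the coders do:

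- Strategies to improve adherence {11c}: "All ERP sessions will be video recorded and 100% will be coded using the Exposure Process Coding System (6) to measure compulsions".
- Exposure Process Coding System (EPCS): "Bachelor’s degree-level study coders will code 80% of video-taped session data". The two shares disagree and should be reconciled, but under either one the coders view most sessions.
- The same EPCS section calls it a "time-stamped coding system that uses Noldus Observer software to capture in-session behaviors as they occur on video". Besides compulsions, the codes cover "youth distress levels (youth-reported and observer-rated; which can index exposure learning").

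The evaluators are in a different position. The outcome-collection section {18a} says they are masked to group, to treatment progress and to the EPCS coding.

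EPCS-coded compulsions are the Phase 1 secondary outcome, the Phase 1 tie-break if both regimens pass (as a rate), and a Phase 2 primary outcome. They are also a proposed mediator of percent change in C/YBOCS: "Compulsion duration and its interaction with the group indicator will be included as potential mediators for the dependent variable".

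**The concern.** The stated means does not achieve the stated end. Keeping a coder out of the room hides nothing that the recording shows. The document therefore credits the coded outcome with a protection it does not have, and no other section supplies it.

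The consequence lies mainly in mediation. A coder who senses that a youth is doing well may be readier to score an ambiguous act as no compulsion, or to end a timed compulsion sooner. The coded mediator then contains a piece of overall improvement. When C/YBOCS change is regressed on that mediator, the two can be associated even if true compulsions play no part. The Objectives say Phase 2 will test the link between target engagement and symptom change, so a spurious association here would bear on a stated purpose of that phase.

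The arm comparison of compulsions is exposed only indirectly, when the arms differ in visible improvement for reasons other than compulsions.

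**Working it through.** **1. The sections side by side.** For the evaluators, absence from sessions plus masking to EPCS coding gives masking to progress. For the coders, absence is followed by viewing 80% or 100% of the recorded sessions. Absence removes nothing from what they see. The reliability threshold (kappa above 0.80), drift monitoring and 10% double-coding in the EPCS section concern agreement. Two coders who share an expectation can agree and both be biased.

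**2. The plan's own figure.** Sample size {14} gives 54 participants after 10% attrition in Phase 2, hence 27 per arm, and 80% power at d = 0.78. A two-sample t-test at two-sided 0.05 (level assumed) gives a detectable d of 0.777, and 80.3% power at 0.78. The figure reproduces, so 27 per arm is used below.

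**3. Mediator term.** Let y be symptom change and e independent noise, with true compulsions unrelated to y. Let the coded value be m = √(1−h)·e + √h·y, where h is the share of coded variance due to coder expectation. The correlation of m with y is √h: √0.02 = 0.14, √0.05 = 0.22, √0.10 = 0.32. All values of h are assumptions. The table shows how often the mediator term is significant at 0.05 (6,000 simulated trials, n = 54):

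| Model | h = 2% | h = 5% | h = 10% |
|---|---|---|---|
| y on group and m; coders perceive C/YBOCS change directly | 18% | 37% | 65% |
| Same, plus the planned interaction (0/1 group coding) and a covariate | 11% | 21% | 37% |
| y on group and m; what coders see correlates 0.5 with C/YBOCS change | 7% | 12% | 20% |
| Same, plus the planned interaction and a covariate | 6% | 9% | 13% |

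With h = 0 the rate is about 5%. The 0.5 correlation is also an assumption. In the third and fourth rows the correlation of m with y falls to 0.5·√h, that is 0.07, 0.11 and 0.16. A joint test of mediator and interaction would give other values.

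**4. A second model, for the arm comparison.** Let coded compulsions = true compulsions − λ × visible improvement, both in SD units, with true compulsions unrelated to arm and to improvement (20,000 simulated trials, 27 per arm). The share of coded variance due to expectation is λ²/(1+λ²): 0.0625/1.0625 = 5.9% for λ = 0.25 and 0.25/1.25 = 20% for λ = 0.5.

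| Arm difference in visible improvement | Arm test, λ = 0.25 | Arm test, λ = 0.5 |
|---|---|---|
| 0 | 4.9% | 4.8% |
| d = 0.5 | 7.4% | 12.7% |
| d = 0.78 | 10.5% | 24.6% |

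The mediator path in this model, adjusted for group, is falsely significant in about 42% (λ = 0.25) and 93% (λ = 0.5) of trials, whether or not the arms differ. Here too coders are assumed to perceive the symptom outcome itself, so these are upper-end values.

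**The case against.** The case on the other side is substantial, and much of it stands.

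- **Arm masking is intact.** A reader might infer that coders could learn the allocation from talk on the recording. The document does not support this. Participants, caregivers, therapists and TMS operators are themselves masked to active versus sham. Half of sham participants receive each stimulation sequence, so hearing about the sequence does not reveal status.
- **No section says that one coder follows a participant through the course.** How videos are assigned, ordered and labelled is not stated, and the coding team's operating procedures may cover it. This limits the likely size. It does not rescue the sentence, which names absence as the device and is wrong for coders.
- **The Phase 1 choice of regimen is not decided by coded duration.** The Objectives use the rate of compulsions, and only if both regimens meet the neural, safety and feasibility criteria. The comparison is between two active arms, so coder expectation matters only if their visible improvement differs.
- **The unblinding rule is not a gap.** A reader might take "IEs will not be intentionally unmasked" to leave coders exposed. The same section limits unmasking to those most critical to the situation, and it concerns arm status, not progress.
- **The simulated sizes follow from the assumed effects.** C/YBOCS scores come from separate evaluators, and coders see only in-session behaviour. The highest figures also omit the planned interaction and covariate.
- **Time-stamped coding to a reliability criterion leaves less room for impression than a global rating.** Some visible progress is simply fewer compulsions, which is the construct being coded and cannot be hidden.

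What remains is that the progress masking stated for coders is not delivered by the means given, and that the agreement checks do not replace it.

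**Conclusion.** The statement is incorrect for coders as written and correct for evaluators. The consequence is limited. With coders masked to arm, the test of compulsions by arm stays near 5% when visible improvement is equal, and rises only if it differs. The Phase 2 mediation analysis is the main exposure. The false-positive rate for the mediator term could be anywhere from slightly above 5% (6% at h = 2% with weak tracking of C/YBOCS change and the planned terms) to well above it (65% at h = 10% with direct perception and no further terms).

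None of these values is a prediction, because the document gives no figure for the expectation effect or for how closely in-session behaviour tracks C/YBOCS change. The direction is clear: a coder who scores improving youths more leniently pushes the result towards apparent mediation. It would go too far to call the coded outcome unblinded, or to quote the upper figures as the expected error rate. The point merits a correction in the text and an inexpensive change to the coding procedure.

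**What to change.** 1. In Who will be blinded {17a}, restrict the absence-based statement about masking to progress to the independent evaluators.
2. In the Exposure Process Coding System section, state that videos carry neutral file names without session number or date, are coded in random order across participants and sessions, and are spread over coders within each participant. Supply each participant's baseline compulsion checklist so that coders know what to look for.
3. Describe the result for coders as reduced exposure to the treatment course. It should not be called ensured masking, because progress visible within one recording cannot be hidden.
4. In the same edit, reconcile the 100% and 80% coding shares.

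The cost is a randomised coding list and some list management. The downside is some loss of coder familiarity with a participant's idiosyncratic compulsions, which the checklist partly offsets. Where Phase 1 coding has begun, the procedure can still apply to videos not yet coded and to all of Phase 2.

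Cutting the recordings to remove conversation is not needed. Sixty participants with ten TMS + ERP sessions each (sessions 2 to 11) make about 60 × 10 = 600 videos per phase. Trimming could also disturb the therapist fidelity codes and the exposure-duration covariate. The unblinding rule needs no extension.

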### Procedure for unblinding if needed {17b}

Intentional unmasking of TMS status (active vs. sham) will be allowable if deemed necessary for participant safety, to address a TMS device issue, or another unforeseen situation in which status knowledge is essential for study conduct. Only individuals deemed most critical for addressing the situation will be unmasked. IEs will not be intentionally unmasked.

## Data collection and management

### Plans for assessment and collection of outcomes {18a}

Study measures, reporters, and administration timing are listed in Table 1. Assessments will be conducted by IEs via HIPAA-compliant video conferencing. IEs will be otherwise uninvolved with the study and will be masked to group assignment, treatment progress, and EPCS coding. IEs will be bachelor’s degree-level research staff trained to criterion to administer all IE measures; they will meet weekly for criterion maintenance and be monitored to prevent drift.

### Measure procedures

#### Exposure Process Coding System (EPCS)

EPCS [6, 36] is an observer-rated, microanalytic, time-stamped coding system that uses Noldus Observer software to capture in-session behaviors as they occur on video. EPCS measures the frequency and duration of youth compulsions during exposure tasks, along with codes measuring therapist behaviors (which serve as an index of treatment fidelity) and youth distress levels (youth-reported and observer-rated; which can index exposure learning). Bachelor’s degree-level study coders will code 80% of video-taped session data. Coders will be trained and monitored to prevent drift. Training will include background reading, group discussions, practice coding with feedback, and practice coding to criterion. Raters must attain reliability on practice videos (*k* > 0.80) before coding study videos. If coder drift is detected, re-training will occur and remaining study videos will not be coded until the reliability criterion is re-established. Ten percent of sessions will be double-coded to assess reliability.

### MRI and fMRI data acquisition

Siemens Prisma 3T scanners located at the Brown University MRI Facility or University of Minnesota Center for Magnetic Resonance Research will be used for image acquisition. Total MRI time will be ~ 1 h for each visit. To minimize motion artifact, we will immobilize the participant’s head with foam padding. We will use Framewise Integrated Real-Time MRI Monitoring (FIRMM) during all functional scans to monitor subject motion in real-time and track the amount of usable data, aiming for ≥ 10 min of data with FD < 0.2 mm, with respiration filter [38]. As needed, we will run additional scan(s) to meet the usability criterion. We will acquire scans using the ABCD pulse sequences, using a multi-echo, multiband BOLD acquisition.A high-resolution volumetric navigator for prospective motion correction [39].Structural scans: whole brain 3D T1-weighted (176 slices, 1 mm isotropic, TE = 2.88 ms, TR = 2500 ms, flip angle = 8°) and whole brain 3D T2-weighted images (176 slices, 1 mm isotropic, TE = 564 ms, TR = 3200 ms), during which participants can watch a movie.Resting state fMRI: whole-brain BOLD-sensitive EPI sequence, multi-echo, multi-band scans (TR = 1761 ms, TE = 14.20/38.94/63.66/88.40 ms, flip angle = 68°, 72 oblique axial slices, 2.0 mm isotropic resolution, Multi-band factor = 6, GRAPPA = 2, 412 volumes, 12 min each). Two 12-min runs will be collected during each visit. Participants will be asked to rest quietly, try to stay awake, and watch a fixation cross.

### MRI and fMRI pre-processing

Functional data will first be denoised with NORDIC [40] and then the multi-echo data will be combined using the “tedana” software package to maximize signal to noise [41]*.* The ABCD-BIDS pre-processing pipelines will be applied to the structural T1 and T2 data as well as the denoised resting state data [42]. Functional time series data will be further preprocessed to reduce artifacts, and subjected to stringent frame censoring and additional nuisance regression to account for potential movement confounds [43]. For analyses, we will extract resting-state BOLD timeseries from an established set of 300 well characterized regions of interest (ROIs) across the whole brain (239 cortical, 34 subcortical, 27 cerebellar) [44] and correlate the timeseries region-by-region to generate brain-wide correlation matrices. pSMA and dlPFC seeds will be the region of interest (ROI). The DLS seed will be ROIs in putamen and the DMS seed will be ROIs in the caudate tail.

### Plans to promote participant retention and complete follow-up {18b}

All study visits will be scheduled in advance, and staff will work with adult participants and parents to problem-solve potential barriers to attending study visits. Family-friendly visit times will be offered as needed. We have also budgeted funds to assist families with transportation costs if that is a barrier. We will implement the Adjunctive Services and Attrition Prevention (ASAP) plan to minimize participant attrition and effectively manage clinical crises that do not meet criteria for study withdrawal, which may occur in RCTs involving a clinical sample. An “ASAP” event is any situation that requires a brief intervention by study staff beyond what is afforded by the assigned treatment arm. Each participant will be allowed one ASAP session during the acute treatment phase.

### Data management {19}

The web-based REDCap system will be used for secure data entry and storage. All entered data will be double-checked by a second staff member, and range checks and missing data flags will be automated. Imaging data will be deidentified and stored on secure servers. A HIPAA-compliant secure storage platform, Box, will be used to store video recordings and data back-ups.

### Confidentiality {27}

Participant information and data will only be accessible to study personnel who (1) have up-to-date human subjects training and certification through the Collaborative Institutional Training Initiative (CITI) curriculum, (2) complete HIPAA and Protected Health Information (PHI) training through their respective institutions, and (3) maintain up-to-date certification on research subject confidentiality and privacy. Data will be labeled using subject ID numbers stored separately from identifying information.

### Plans for collection, laboratory evaluation and storage of biological specimens for genetic or molecular analysis in this trial/future use {33}

Not applicable as biological specimens will not be collected.

## Statistical methods

### Statistical methods for primary and secondary outcomes {20a}

#### Phase 1

##### Primary outcome (connectivity in targeted circuit)

Seed-based analyses [44] will test RSFC between a priori identified ROIs (as described above) and use a false discovery rate (FDR) correction for multiple comparisons threshold of *p* < 0.05. ROI correlation matrices will be converted to individual *Z*-scores using Fisher’s transformation, yielding indices representing RSFC in each targeted network. To test if active rTMS has a within-subject effect on RSFC, we will conduct paired *t*-tests for the change in RSFC for each active rTMS group within the targeted network (pSMA-DLS for cTBS arm, dlPFC-DMS for iTBS arm). We will conduct two separate two-sample *t*-tests for the group effect of rTMS: one for iTBS (dlPFC) vs sham and one for cTBS (pSMA) vs sham.

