Primary outcomes focus on neural change and will be indexed by within-subject (pre- to post-treatment) and between-subject (iTBS vs. sham; cTBS vs. sham) change in fMRI-measured RSFC between the targeted network (pSMA-DLS for cTBS arm, dlPFC-DMS for iTBS arm). We will also examine several other outcomes. First, we will evaluate between-subject differences in compulsions during ERP (rate per session as observed by independent raters using EPCS). We will assess safety at baseline, post-treatment, daily treatment sessions, and 1-month follow-ups using the staff-administered Adverse Events Questionnaire (TMS AEQ), aggregated as the number of treatment-related adverse events and tolerability ratings of side effects. We will assess feasibility at post-treatment, based on treatment completion rate (percent of participants completing ≥ 80% of treatment sessions).

#### Phase 2

The primary outcomes are neural change (RSFC in the targeted circuit as in Phase 1) and change in compulsion rate (rate per session as in Phase 1). These will be indexed by within-subject (pre- to post-treatment) and between-subject (active vs. sham) change. We will also examine whether changes in neural and behavioral outcomes mediate change in OCD symptom severity (percent change in C/YBOCS total score from pre- to post-treatment). Secondary analyses will examine (1) the relationship between pre-treatment clinical measures and OCD symptom change, and (2) subgroup effects in primary outcomes, and (3) durability of change in primary outcomes through 1-month follow-up.

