### Participant timeline {13}

Participant activities are depicted in Fig. 1. Participants who meet initial eligibility criteria on the phone screen (Gate A) will be scheduled for the clinical interview (Gate B), at which time the consent/assent and Gate B measures will be completed and final eligibility determined. The baseline assessment (Gate C), which involves the pre-treatment MRI scan, will be completed within 1 calendar month of Gate B. The daily treatment sessions will begin within 5 calendar days of completing Gate C (to allow for running and checking the TMS targeting pipeline). Participants will complete the 12 TMS + ERP treatment sessions (Fig. 2) within 15 business days. The mid-treatment assessment will occur between sessions 6 and 7. The post-treatment assessment will be completed within the 10 calendar days following the last treatment session, with a targeted window of 1–3 business days. The post-treatment MRI scan will occur at least 24 h after the last TMS session to avoid capturing the acute aftereffect of TMS. The 1-month assessment will be completed 4–6 weeks after the last treatment session.

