### Assignment of interventions: allocation

#### Sequence generation {16a}

Block randomization, stratified on site (Brown or UMN) and baseline OCD severity (C/YBOCS total < 32 vs. > = 32), will be performed using the blockrand package in R [37].

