##### Primary outcome (connectivity in targeted circuit)

Following procedures outlined for this outcome in Phase 1, a two-sample *t*-test will assess the difference in RSFC in the targeted circuit pre- and post-treatment for active rTMS vs sham. A linear regression model will also be used with the outcome of interest being the percent change in OCD symptom severity (C/YBOCS) pre- and post-treatment. The primary predictor will be a group indicator for sham vs active TMS. Differences pre- and post-treatment in RSFC and its interaction with the group indicator will be included as potential mediators for the dependent variable.

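### The primary RSFC group comparisons are unadjusted t-tests on change, which are valid but give up precision that baseline RSFC and the randomisation strata could supply

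*Protocol article*

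**What the plan says.** All references are to the protocol article.

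- **Phase 1 test.** Under Statistical methods {20a}, Phase 1, Primary outcome, the between-group analysis is two two-sample t-tests "for the group effect of rTMS: one for iTBS (dlPFC) vs sham and one for cTBS (pSMA) vs sham". No covariate is named, and this sentence does not itself name the dependent variable.
- **What is compared.** Outcomes {12} settles that: the between-group outcome is "between-subject (iTBS vs. sham; cTBS vs. sham) change in fMRI-measured RSFC between the targeted network", with pSMA-DLS as the circuit for cTBS and dlPFC-DMS for iTBS.
- **Phase 2 test.** The corresponding Phase 2 section follows the Phase 1 procedures and uses a two-sample t-test to "assess the difference in RSFC in the targeted circuit pre- and post-treatment for active rTMS vs sham".
- **Randomisation.** Sequence generation {16a} describes block randomisation "stratified on site (Brown or UMN) and baseline OCD severity", with severity cut at a C/YBOCS total of 32.
- **Scanners.** Images come from "Siemens Prisma 3T scanners located at the Brown University MRI Facility or University of Minnesota Center for Magnetic Resonance Research", so site and scanner coincide.
- **Baseline data.** Participant timeline {13} and Table 1 place an MRI scan before and after treatment.
- **Covariates elsewhere.** The compulsion-duration analysis is a regression with total exposure duration as covariate.
- **Use of the estimate.** Objectives {7} makes a between-subject RSFC effect of at least d = 0.3 one of the conditions for opening Phase 2.

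**The concern.** A change-score t-test uses baseline only by subtraction, which fixes its slope at 1. When the true regression of post-treatment on baseline RSFC is flatter than that, subtraction adds noise, and chance baseline imbalance between arms carries into the estimate through regression to the mean. Analysis of covariance estimates the slope.

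The strata are a separate matter. Where randomisation has balanced the arms on a factor that predicts the outcome, leaving it out overstates the standard error.

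Phase 1 is expected to yield about 18 analysed participants per arm. A point estimate from those numbers helps to decide whether Phase 2 opens and with which regimen, and the same form of test is a Phase 2 primary analysis. Precision available from data already being collected is worth having.

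**Working it through.** **Inputs.** From Trial design {8} and Sample size {14}: 60 participants per phase, 10% attrition, 54 analysed, so 54/3 = 18 per arm in Phase 1 and 54/2 = 27 in Phase 2. Stated detectable effects at 80% power: d = 0.70 to 0.96 in Phase 1 and 0.78 in Phase 2. Assumed, because the article does not state them: two-sided alpha of 0.05 for the power calculation, equal pre and post SDs, and r between 0.3 and 0.9.

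**Step 1: reproduce the plan's figures.** With noncentral t at two-sided 0.05, the effects detectable with 80% power are 0.701 (paired, n = 18), 0.961 (18 vs 18) and 0.777 (27 vs 27). These match 0.70, 0.96 and 0.78. A one-sided test would give 0.846 for 18 vs 18, which does not match. The power statement therefore describes plain t-tests and credits no adjustment.

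- Phase 1: noncentrality 0.96 × √(18/2) = 2.88 on 34 df, power 79.9%.
- Phase 2: noncentrality 0.78 × √(27/2) = 2.87 on 52 df, power 80.3%.

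**Step 2: variance ratio.** With common SD σ, the variance of change is 2σ²(1−r), and the residual variance after adjustment for baseline is σ²(1−r²). The ratio is (1−r²)/[2(1−r)] = (1+r)/2. With unequal SDs s₁ (pre) and s₂ (post), the change-score variance minus the adjusted variance is (s₁ − r·s₂)², which is never negative.

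**Step 3: power with adjustment.** Divide the noncentrality by √((1+r)/2) and take off three df (baseline, site, severity). No variance reduction is credited to the strata, and d stays in SDs of change.

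| r | Variance ratio | Equivalent extra participants | Phase 1 power (d = 0.96) | Phase 2 power (d = 0.78) |
|---|---|---|---|---|
| as planned | 1 | – | 79.9% | 80.3% |
| 0.3 | 0.65 | 54% | 93.3% | 93.6% |
| 0.5 | 0.75 | 33% | 89.6% | 90.0% |
| 0.7 | 0.85 | 18% | 85.7% | 86.1% |
| 0.9 | 0.95 | 5% | 81.7% | 82.2% |

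The extra-participants column is 1/ratio − 1.

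**Step 4: the strata alone.** Adding site and severity to a change-score analysis at 18 vs 18 and d = 0.96 gives power of 79.7%, 81.7%, 83.7% or 87.7% if they explain 0, 5, 10 or 20% of the variance of change. The article gives no such share.

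**Step 5: the scanner.** Simulation with 18 per arm, sites balanced, r = 0.5 and 5,000 runs per scenario:

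- A constant 1-SD scanner offset leaves the change-score test at about 79% power and 4.9% type I error, because the offset cancels.
- A 0.5-SD site difference in change itself lowers type I error to about 4.2%.
- The model with baseline and site holds about 88–89% power and 4.6–4.9% type I error in every scenario, close to the 89.6% in the table.

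**Step 6: the Go/No-Go threshold.** By normal approximation the SE of the planned between-subject d is √(2/18) = 0.333, so an arm with no effect reaches 0.3 with probability 1 − Φ(0.3/0.333) = 18.4%. If the adjusted difference is divided by the SD of change, the SE shrinks by √((1+r)/2), and that probability is 13.2%, 14.9%, 16.4% or 17.8% for r = 0.3, 0.5, 0.7 or 0.9. At a true d of 0.6, the chance of reaching 0.3 rises from 81.6% to 86.8%, 85.1%, 83.6% or 82.2%. If the residual SD is used as divisor instead, the threshold in change-score SDs drops to 0.3 × √((1+r)/2) = 0.24, 0.26, 0.28 or 0.29, and the false-pass probability stays at 18.4%.

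**The case against.** The best defence is that nothing here is wrong. The planned test is valid, the stated detectable effects follow from it exactly, and choosing it over covariance adjustment is a matter of efficiency. That stands, and it limits the point to a recommendation.

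Three stronger readings are tempting, and the documents do not support them.

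- **That baseline RSFC is ignored.** Outcomes {12} and the Phase 2 section define the comparison on pre-to-post change, so baseline enters by subtraction. The gain is therefore the modest one in Step 3, not the gain over a test of post-treatment values alone.
- **That scanner differences distort the result.** Both sites use the same scanner model, and a constant offset cancels in a change score. Only a site difference in change itself would matter, and the effect simulated was slight conservatism.
- **That adjusting for the strata is bound to help.** This depends on whether they predict change in RSFC. If they do not, power slips from 79.9% to 79.7%.

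It can also be said that covariates are commonly left to an analysis plan that is not shown. For unnamed stratum terms alone, that would be a fair answer. Here, however, the article names a test that admits no covariates, repeats it for Phase 2, and does name a covariate in the compulsion model.

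Finally, power at d = 0.96 says little about a rule set at d ≥ 0.3. That is correct, and it is why Step 6 treats the rule separately and why the divisor must be fixed.

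**Conclusion.** The point holds as one of precision. The expected gain in power for the primary between-group comparison runs from about 2 percentage points (r = 0.9) to about 13 (r = 0.3) in both phases. It rests on the assumed range of r, equal pre and post SDs, a two-sided 5% level and the attrition stated in the plan. A benefit from the strata beyond this is possible but cannot be sized from the article. The benefit for the Go/No-Go rule is smaller: 0.6 to 5.2 percentage points off the false-pass probability for the between-subject part, and only if d is scaled by an unadjusted SD. The within-subject part of the rule is unaffected. The change should be made, but the trial's validity does not depend on it.

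**What to change.** In the primary connectivity sections for both phases, replace the two-sample t-tests with a linear model of post-treatment Fisher-z RSFC on arm, baseline RSFC of the same circuit, site and severity stratum. Fit it separately for each targeted circuit: pSMA-DLS for cTBS vs sham and dlPFC-DMS for iTBS vs sham in Phase 1, and the selected circuit in Phase 2. A single three-arm model would not serve, because the two contrasts have different outcomes.

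In Objectives {7}, state that the between-subject d is the adjusted difference divided by a prespecified unadjusted SD, for example the pooled SD of change, so that adjustment does not silently lower the 0.3 threshold.

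The cost is revised wording and about three degrees of freedom (34 to 31 in Phase 1, 52 to 49 in Phase 2). No new data are needed, and the present sample-size statement can stand as the unadjusted case.
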